## Abstract

**Background:** Several exercise methods with virtual reality devices have been used in treatments for older adults and patients with neurodegenerative diseases, although the mechanisms continue to be elucidated. The aim of this study is to establish the feasibility and effectiveness of a rehabilitation programme using low-cost virtual reality aimed at improving postural balance in older adults. It also seeks to compare low-cost virtual reality under two delivery modalities, telerehabilitation (TR) in elderly centres and face-to-face (FtF) in rehabilitation centres. **Methods:** The study is set up as a non-inferiority two-arm parallel triple-blind randomised controlled clinical trial. Sixteen persons aged 65 to 75-years-old will be included. Eighteen Wii therapy sessions (25–30 min) will be provided through both FtF (control group, *n* = 8) and TR (exposure group, *n* = 8), both with a Nintendo Wii balance board. Data will be collected at baseline (week 0), during the Wii therapy sessions (weeks 2, 4, and 6), and during the follow-up (weeks 8 and 10). The primary outcome will be the area of centre-of-pressure (CoP) sway; secondary outcomes will be medial–lateral and anterior–posterior velocity and standard deviation of CoP; and tertiary outcomes will be clinical measures: single-leg stand, timed up-and-go tests, Barthel Index, and Tinetti’s scale. Statistical analyses will be performed using SPSS 20.00 for Windows. The trial adheres to the Declaration of Helsinki and the Chilean laws of rights and duties of the patient and research in humans. Ethical approval was obtained from the Ethics Committee of the University of Talca. Written informed consent will be obtained from participants. **Discussion:** In this trial, older adults from a Chilean city with a large rural and underserved population share will be included to test the feasibility and effectiveness of a rehabilitation programme using low-cost VR aimed at improving postural balance to generate evidence to support decision makers generating public health policy. **Trial registration:** Australian New Zeeland Clinical Trials Registration (ACTRN12621001380886).

## 1. Background

One of the most affected motor skills in the elderly population is the loss of postural balance, accentuating the risk of falls and a series of traumatic events that include hip fracture [1]. For several years, many countries in the world promoted the importance of physical exercise in older adults and its beneficial effects for postural balance, functional mobility, and quality of life [2,3,4]. Chile, one of the first Latin American countries to lead the development of public policies and physical activity programmes in communities for the elderly [5], has had to stop these programs because of the COVID-19 pandemic. Among the strategies to stop the advance of COVID-19 has been restricting movement of the general population. In line with this, many countries turned to restrictive policy measures where the freedom of movement of their citizens was limited [6]. Confinement strategies can accentuate the effects of physiological aging in the elderly population, leading the individual to a greater functional decline in their daily activities further deteriorating the loss of postural balance and its consequences [7]. It is well known that during aging cognitive and motor functions may be influenced by peripheral and central degenerative phenomena such as decreased neuroplasticity and sarcopenia [8,9,10]. 

Physical exercise has been widely recognised for its numerous benefits in the older adult population. It enhances neural function, cardiopulmonary performance, physical integration, respiratory muscle performance [11,12,13], postural balance [14,15,16,17], and immune system activity [18,19]. However, besides the benefits of physical exercise [20], an important part of the world population remains physically inactive, especially older adults [21], which has been aggravated by the application of confinement strategies that limit the possibility of carrying out guided physical activity in this population [6]. Therefore, creating home movement strategies for older people is a priority. 

Respiratory diseases that affect the elderly not only affect inspiratory muscles but also negatively affect postural balance in this population, accentuating the risk of falls and their traumatic consequences [22]. These findings are key to consider to prevent the physical sequelae of respiratory diseases, which are accentuated by voluntary or compulsory confinement in this population. Ferraro et al. [22] proved that unsupervised physical inspiratory muscles training at home twice each day for 8 weeks significantly improved not only inspiratory muscle function but also postural balance in older adults. Physical exercise is essential for older adults to keep good postural balance, which helps avoid the diverse physical complications caused by lockdown.

Several exercise methods with virtual reality (VR) devices have been used in treatments for older adults and patients with neurodegenerative diseases [23,24,25,26]. Interfaces have been created to be used in computer or available electronic games that generate communication between the user and the virtual environment through body movements. The main widely known commercial devices are Nintendo Wii and Xbox 360 Kinect [25]. Interventions with these devices are based on exercise execution where the individual receives sensory stimuli (extrinsic feedback), mainly visual information, to increase the amount of input to allow motor self-adjustments. The use of these technologies seems to improve postural balance of older people, neurological and stroke patients, and patients with Parkinson’s disease [23,24,25,26,27]. Although the mechanisms still remains unclear, VR rehabilitation therapy shows a positive tendency to improve mental and physical health [27,28,29,30].

The recognition of VR-based therapies as accessible and low-cost systems primarily applies to developed or high-income countries [31,32]. However, that is not the situation in low- and middle-income countries (LMIC), underserved populations, and rural settings. For example, high-end VR headsets usually cost USD 600–800, not including the computer or console to connect with. In that regard, some researchers and developers are working to create low-cost VR devices focused on rehabilitation [33,34]. However, development and validation usually take many years until a product is released to the market. Thus, low-cost and available VR systems appear as a relevant option to be considered in LMIC in order to expand VR-based rehabilitation therapies. Nintendo Wii has proven to be an efficient and effective system to implement VR-based therapies in many settings [35,36,37,38]. Moreover, used or refurbished Nintendo Wii consoles and balance boards can be purchased online for USD 100–200. 

The benefits of VR-based therapies in older people and other populations have been demonstrated in in-person or face-to-face modalities, where a physiotherapist typically guides the therapy [23,24,25,26]. However, the COVID-19 pandemic has limited the access to those modalities, which spotlights telerehabilitation (TR) as a necessity to maintain rehabilitation therapies. However, the evidence on TR and VR rehabilitation is scarce, a recently published systematic review on this matter found only seven randomised clinical trials and concluded that VR and TR can be used as a prolongation to conventional therapy [25].

The aim for this study is to establish the feasibility and effectiveness of a rehabilitation programme using low-cost VR aimed at improving postural balance in older adults. It also seeks to compare low-cost VR under two delivery modalities, TR in elderly centres and face-to-face (FtF) in rehabilitation centres.

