## 2. Method

### 2.1. Design

This is a non-inferiority randomised, triple-blind, controlled clinical trial. Reporting follows Standard Protocol Items: Recommendations for Interventional Trials (SPIRIT [39], see Supplementary File). Figure 1 provides an overview of the trial design. 

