### 2.2. Study Setting

This research study examines the impact of low-cost virtual reality in two distinct environments. The first environment is a clinical setting, specifically the Telerehabilitation Technology Centre and Neurosciences in Human Movement at Universidad de Talca in Talca, Chile. In this setting, a low-cost virtual reality intervention is provided in a face-to-face format with a therapist directly interacting with the patient (FtF modality, control group). The second environment is a remote facility, where there is no therapist present, and a low-cost virtual reality intervention is delivered through TR. This will take place in two elderly centres, and the choice of location will be based on the participants’ access to equipment and space. The assessments will be conducted at the facility where the therapy was performed.

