### 2.5. Interventions

The objective of this study is to evaluate and contrast the outcomes resulting from the implementation of affordable virtual reality technology across FtF and TR modalities. The low-cost virtual reality intervention entails the utilization of a Nintendo Wii balance board, facilitating the engagement of participants in four exergames.

The FtF group will receive training from a physiotherapist at the telerehabilitation centre of Universidad de Talca, specifically designed for elderly patients. In contrast, the TR group will be trained by an older adult who has undergone six months of training in the rehabilitation program using low-cost virtual reality. These trained older adults will act as therapists for their peers, who belong to two senior citizen centres located near their homes. These centres offer recreational and sports activities for older adults who attend daily. The elderly therapist will receive remote guidance from the telerehabilitation centre at Universidad de Talca, Chile.

FtF and TR groups will undergo a total of 18 sessions, which will be delivered over a period of 6 weeks, with a frequency of 3 times per week (Monday, Wednesday, and Friday) for 25 min per session, followed by four weeks of follow-up for the older adults. For the first 3 weeks, each participant will perform three sets of exercises with manual guidance and verbal instructions. Subsequently, only verbal instructions will be provided by a physiotherapist or elderly therapist. The rehabilitation program has three sets of exercises that improve postural balance in the sagittal, frontal, and transversal planes of motion. The games used in the first two sets of exercises are Snowboard, Penguin Slide, and Super Hula Hoop, while the Yoga game is used in the third set. In the first set of exercises, the older adults will stand in a relaxed position with their arms and hands at their sides. In the second set of exercises, each game will be repeated in a standing position with their hands on their waists. Between the first and second sets of exercises, a one to two minute break will be given, during which the participants will sit on a chair until they have recovered. The third set of exercises involves maintaining a relaxed posture during the Yoga game with their eyes open and then repeating it with their eyes closed.

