### 2.11. Data Analysis

Statistical analyses will be conducted using SPSS 20.00 for Windows. Descriptive statistics will be utilised to determine the demographic and clinical characteristics of participants in both groups (unpaired *t*-tests and χ^2^ tests). 

The normality and homogeneity of variance of all outcome measures will be assessed using the Shapiro–Wilk and Levene tests, respectively. If the assumptions of normality are met, a t-test will be employed, otherwise, the Mann–Whitney U test will be used to determine differences between the FtF and TR groups. Additionally, if the assumptions of normality are fulfilled, a repeated measures analysis of variance (RM-ANOVA) will be employed, otherwise, Friedman’s test will be used. Post hoc pairwise comparisons will be used to determine the intervention’s effect over time for each group (FtF and TR). Cohen’s d will be used to report effect sizes for the CoP variables. To allow repeated measures analysis, missing data will be adjusted by (1) replacing with the non-missing average values for each variable/week and (2) performing multiple imputations. Both methods will be used to make sure that the results are concordant. For all analyses, a *p*-value ≤ 0.05 will be considered statistically significant. All statistical analyses will be performed using IBM-SPSS 20.0 (SPSS Inc., Armonk, NY, USA).

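### With the Wii programme in both arms, within-group change cannot establish its effectiveness, and the randomised contrast compares two delivery packages, not remote delivery as such

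*Protocol article*

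**What the plan says.** Section 1 (Background) gives two aims. The first is "to establish the feasibility and effectiveness of a rehabilitation programme using low-cost VR aimed at improving postural balance in older adults". The second is added to it: "It also seeks to compare low-cost VR under two delivery modalities, TR in elderly centres and face-to-face (FtF) in rehabilitation centres". The Abstract and section 4 (Conclusions) repeat the first aim, and both link it to evidence for public health policy.

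Section 2.1 states the design: "This is a non-inferiority randomised, triple-blind, controlled clinical trial". Section 2.5 gives both arms the same programme: "FtF and TR groups will undergo a total of 18 sessions". No arm is untreated, on usual care or on other exercise. The sample size in section 2.3 concerns the difference between FtF and TR only.

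Section 2.11 plans between-group tests and a repeated-measures analysis, and then: "Post hoc pairwise comparisons will be used to determine the intervention’s effect over time for each group".

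On the content of the arms, section 2.5 says: "The FtF group will receive training from a physiotherapist at the telerehabilitation centre of Universidad de Talca". It continues: "In contrast, the TR group will be trained by an older adult who has undergone six months of training in the rehabilitation program". These older adults are said to act as therapists, and the remote guidance from the university centre goes to them. Section 2.2 describes the TR setting differently: "The second environment is a remote facility, where there is no therapist present". It also places each participant's assessments at the facility where that participant was treated.

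**The concern.** Effectiveness of the programme is a separate aim, but the design has no contrast that isolates it. Section 2.11 fills the gap by treating before/after change within each arm as the effect of the intervention. If the plan is followed, uncontrolled change in 16 people would be reported as evidence that the programme works.

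The second aim has a narrower problem. Section 3 (Discussion) anticipates that the TR modality will be non-inferior. The TR arm, however, changes the trainer and the site as well as adding remote guidance, and the article is inconsistent about whether anyone acting as therapist is in the room. A policy reader could take a favourable result as showing that remote therapy matches a physiotherapist, when what was tested may have been a trained peer on site with remote backing.

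**Working it through.** **1. What the trial is sized for.** Inputs from section 2.3: difference 1.5, SD 1, alpha 0.05 (taken as two-sided), power 80%, attrition 5%.

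n per arm = 2(z₀.₉₇₅ + z₀.₈₀)² × SD² / difference² = 2(1.960 + 0.842)² × 1 / 2.25 = 6.98, rounded up to 7. With attrition: 7 / 0.95 = 7.37, rounded up to 8, or 16 in total.

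The stated figure reproduces. Reading 1.5 as a non-inferiority margin with true difference 0 and one-sided 0.025 also gives 7, then 8. Either way the inputs describe FtF versus TR. No figure concerns programme versus no programme.

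**2. What can be identified.** Let P_F and P_T be the programme effects in the two arms, and S the change that time and repeated testing would produce anyway.

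- Mean change, FtF = P_F + S
- Mean change, TR = P_T + S
- Difference = P_T − P_F

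There are two means and three unknowns. The difference is identified. P_F and P_T are not, unless S is known or assumed to be zero. If S differs because assessments take place at different sites, that difference becomes part of the package contrast.

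S is unlikely to be zero. There are six assessments (baseline and weeks 2, 4, 6, 8 and 10; section 2.6). The eight posturographic tasks in section 2.10 include playing Snowboard and Penguin, both of which are trained in section 2.5.

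**3. How large the problem could be (assumed shifts).** Take P = 0, and let S be d standard deviations of the change score. The chance of a significant paired t-test (two-sided 5%, noncentrality d√n, n − 1 degrees of freedom) is:

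| d (assumed) | one arm, n = 8 | both arms pooled, n = 16 |
|---|---|---|
| 0 | 5% | 5% |
| 0.3 | 11% | 20% |
| 0.5 | 23% | 46% |
| 0.8 | 50% | 85% |
| 1.0 | 68% | 96% |

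The article gives no value for d, so this shows a range and is not an estimate.

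**4. What differs between the arms.**

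| | FtF | TR |
|---|---|---|
| Trainer (2.5) | physiotherapist | trained older adult |
| Site (2.2, 2.5) | university centre | two senior centres |
| Place of assessment (2.2) | university centre | senior centres |
| Remote element (2.5) | none described | guidance to the peer trainer |

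All rows change together, so only their sum is estimated. To illustrate, assume a margin of 1.5, SD 1, 8 per arm and one-sided 0.025, and suppose remote delivery alone were worse by the full 1.5. If trainer or site offsets b of that deficit, the noncentrality is b / √(2/8) = 2b with 14 degrees of freedom:

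| b (assumed) | non-inferiority concluded |
|---|---|
| 0 | 2.5% |
| 0.5 | 15% |
| 1.0 | 46% |
| 1.5 | 80% |

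These findings are not errors about the packages, because the package deficit really is 1.5 − b. They would be errors only if read as statements about remote delivery.

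**5. Who is present in the TR arm.** Section 2.2 separates the arms by whether a therapist is there. Section 2.5 has peers acting as therapists in the TR arm and gives every participant manual guidance for the first three weeks. Manual guidance implies physical presence; this is an inference, since the article does not say so outright. The two sections do not fit together as written.

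**The case against.** The strongest defence is that a non-inferiority trial against an active comparator normally has no untreated arm. The Background says that benefits of VR therapy have been shown face to face and that the Wii is effective, so the TR arm would inherit effectiveness through the comparator. That stands as a justification of the design: the missing third arm is not in itself a fault. It does not support the stated aim. Effectiveness would then rest on outside evidence that this trial does not test, since two equally ineffective arms would also look non-inferior. The Background describes that evidence as coming from therapy typically guided by a physiotherapist, which is not the TR arm. Section 2.11 also draws the effect from within-group tests and not from this indirect argument.

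It can also be said that section 2.2 means only that no professional therapist is present. That is plausible, but the text does not say it.

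A reader might infer more than the article supports:

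- **That TR versus FtF cannot be answered.** It can. Allocation is randomised 1:1, the comparison of whole packages is identified, and sections 1 and 2.5 largely describe the arms in those terms.
- **That within-group change reflects regression to the mean.** Section 2.4 has no balance or sway threshold, so there is little basis for this.
- **That the number of post hoc tests measures the defect.** Multiplicity is a separate matter. The article does not say which visit pairs are tested, whether an omnibus test comes first, or whether p-values are adjusted, and a control arm would not change the count.
- **That feasibility is left unmeasured.** Section 2.6 lists no feasibility outcome, but definitions and thresholds may sit in the full protocol.

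**Conclusion.** The concern holds in two limited respects. First, the aim of establishing effectiveness cannot be met by the planned within-group comparisons, and section 2.11 is wrong to label their result the intervention's effect. A statistical analysis plan that is not shown could not repair this, because it cannot supply a comparator. Second, the TR-versus-FtF result is valid for the two packages as delivered but cannot be credited to remote delivery as such.

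The size depends on quantities the article does not give. Under assumed retest shifts of 0.3 to 1.0 SD of the change score, an ineffective programme would show a significant paired change in 11% to 68% of arms of 8, and in 20% to 96% of trials with both arms pooled. Practice on trained games bears directly on two of the eight tasks; time and general retest effects bear on all of them. The sample size is unaffected. What changes is what the trial may conclude, which matters because the Conclusions offer the result to policy makers.

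**What to change.** 1. In the Abstract, section 1 and section 4, drop the claim to establish effectiveness of the programme. Restate the aim and conclusions as a comparison of two delivery packages: peer-led with remote guidance in senior centres, and physiotherapist-led at the university centre. Word the non-inferiority expectation in section 3 in the same terms.
2. In section 2.11, replace the sentence on post hoc comparisons. Within-arm change should be reported descriptively with confidence intervals, and the text should say that it is uncontrolled and is neither the intervention's effect nor evidence of effectiveness.
3. Reconcile sections 2.2 and 2.5 on who is present during TR sessions and what the remote link consists of, so that the package label in step 1 is accurate.

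None of this needs extra participants, visits or measurements. The cost is a narrower claim. Keeping the effectiveness aim would require a comparator without the programme, and the article gives no inputs from which to size one.

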## 2. Method

### 2.1. Design

This is a non-inferiority randomised, triple-blind, controlled clinical trial. Reporting follows Standard Protocol Items: Recommendations for Interventional Trials (SPIRIT [39], see Supplementary File). Figure 1 provides an overview of the trial design. 

### 2.2. Study Setting

This research study examines the impact of low-cost virtual reality in two distinct environments. The first environment is a clinical setting, specifically the Telerehabilitation Technology Centre and Neurosciences in Human Movement at Universidad de Talca in Talca, Chile. In this setting, a low-cost virtual reality intervention is provided in a face-to-face format with a therapist directly interacting with the patient (FtF modality, control group). The second environment is a remote facility, where there is no therapist present, and a low-cost virtual reality intervention is delivered through TR. This will take place in two elderly centres, and the choice of location will be based on the participants’ access to equipment and space. The assessments will be conducted at the facility where the therapy was performed.

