### 2.9. Management

At the beginning of the study, participants will be informed about their random assignment to either the FtF or TR group. To ensure engagement and compliance, older adults in both groups will be regularly asked about the content of the interventions they receive. Data entry will be conducted by an employee outside the research team, who will use separate datasheets to prevent researchers from accessing information about group allocation during data analysis.

The raw data will be stored electronically in encrypted text files, while the calculated and clinical outcome measures will be saved in an encrypted Excel spreadsheet. To ensure data security and prevent loss, backups will be created on a weekly basis.

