### 2.10. Data Collection

All measurements will be conducted under identical conditions and by the same assessor at each time point, at a consistent time of day. Posturographic assessments (CoP displacements) for both groups will be obtained utilizing an AMTI OR67 force platform (Watertown, MA, USA). AMTI NetForce software (Watertown, MA, USA) will be utilised for the acquisition of moments and forces at a rate of 100 Hz. Data will be recorded, assigned a code, and saved on a personal computer. CoP variables will be determined using Matlab R2022 (Mathworks Inc., Natick, MA, USA).

All primary and secondary posturographic measures will be evaluated across eight distinct postural tasks, each lasting 60 s, except for the dynamic postural task which will last 30 s. The postural tasks will comprise two static conditions: (i) standing motionless with eyes open, and (ii) standing motionless with eyes closed. In addition, six dynamic conditions will be evaluated: voluntary sway in the mediolateral direction, following a metronome set at 30 Hz ((i) and (ii)) and 60 Hz ((iii) and (iv)), with eyes open and closed for each frequency. Multidirectional sway will also be assessed while playing two different videogames that challenge (v) anterior–posterior postural control (Snowboard, 30 s) and (vi) medial–lateral postural control (Penguin). It is anticipated that all assessments, including clinical evaluations, will be completed within 40 min.

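### Assessing each participant where therapy was given aligns place of measurement with arm, and triple-blind does not describe this design

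*Protocol article*

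**What the plan says.** Section 2.2 (Study Setting) gives each arm its own location. For FtF, the control: "The first environment is a clinical setting, specifically the Telerehabilitation Technology Centre and Neurosciences in Human Movement at Universidad de Talca in Talca, Chile". For the TR arm: "This will take place in two elderly centres, and the choice of location will be based on the participants’ access to equipment and space". Section 2.2 then ends: "The assessments will be conducted at the facility where the therapy was performed".

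Section 2.10 (Data Collection) says: "All measurements will be conducted under identical conditions and by the same assessor at each time point, at a consistent time of day". On the device it says: "Posturographic assessments (CoP displacements) for both groups will be obtained utilizing an AMTI OR67 force platform". It does not say whether one platform is moved, several are used, or they are calibrated against each other.

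On blinding, section 2.1 (Design) says: "This is a non-inferiority randomised, triple-blind, controlled clinical trial". The abstract uses the same label. Section 2.9 (Management) says that at the start "participants will be informed about their random assignment to either the FtF or TR group". The only masking measure described there concerns data entry and analysis. Section 2.5 has FtF sessions led by a physiotherapist and TR sessions by a trained older adult.

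The primary outcome (section 2.6.1) is centre-of-pressure (CoP) sway area, with higher values worse. Participants are measured six times: baseline and weeks 2, 4, 6, 8 and 10 (section 2.6).

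**The concern.** There are two separate problems.

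The first is place of measurement. The two arms share no therapy location, so testing people where they were treated means the arms share no test location either. Anything about the place that shifts CoP area, such as floor, platform mounting, surroundings or game set-up, would enter the TR minus FtF difference in post-treatment values. Stratifying randomisation by site (section 2.8) does not help, because arm decides where a person is tested. The place also tells the assessor the arm. That matters most for the clinical tests (Tinetti, single-leg stance, timed up-and-go, Barthel Index), where instruction, timing or judgement plays a part.

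The second is the blinding label. A reader of the abstract or section 2.1 would credit the trial with a protection that section 2.9 removes. This holds whatever is decided about place.

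**Working it through.** **1. Passages side by side: place**

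| Arm | Therapy (2.2) | Assessment (2.2) |
|---|---|---|
| FtF | University centre only | University centre |
| TR | Two elderly centres only | One of the two elderly centres |

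The arms have no test place in common. Section 2.10 nevertheless promises identical conditions for all measurements.

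**2. Passages side by side: blinding**

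| Role | What the article supports |
|---|---|
| Participant | Told the arm (2.9) |
| Trainer | Knows the arm from the role itself (2.5) |
| Assessor | No masking described; the place reveals the arm (inference from 2.2) |
| Data analyst | Masked through separate datasheets (2.9) |

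Three masked roles cannot be found.

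**3. The plan's own figure**

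Inputs from section 2.3: difference 1.5, SD 1 cm², alpha 0.05 (taken as two-sided), power 80%, attrition 5%.

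n per arm = 2 × (1.96 + 0.84)² × 1² / 1.5² = 15.68 / 2.25 ≈ 6.97, so 7. With attrition, 7 / 0.95 = 7.37, so 8 per arm and 16 in total. The stated sample size reproduces, and nothing below changes it.

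**4. What a place offset would do (illustration)**

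The documents give no offset, so the values below are assumed. Other assumptions are no true arm difference, SD 1 cm², 8 per arm, and an unadjusted two-sided t-test on post-treatment values.

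Standard error of the difference = √(2 × 1² / 8) = 0.5 cm². Degrees of freedom = 8 + 8 − 2 = 14. Noncentrality = offset / 0.5. The rejection rate comes from the noncentral t distribution.

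| Assumed offset (cm²) | Noncentrality | Two-sided false-positive rate |
|---|---|---|
| 0 | 0 | 5.0% |
| 0.25 | 0.5 | 7.5% |
| 0.5 | 1.0 | 15.4% |
| 0.75 | 1.5 | 28.7% |
| 1.0 | 2.0 | 46.1% |

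An offset of 1.0 cm² equals the whole planning SD and should be read as an extreme case.

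**5. When the offset cancels**

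Let a place add a constant d to every value measured there.

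- Post-treatment value: true value + d. The arm difference carries d in full.
- Change from baseline, both taken at that place: (follow-up + d) − (baseline + d). The d disappears.
- Change from baseline, with baseline taken elsewhere: d remains in full.
- Baseline as a covariate with slope b, both taken at that place: d − b × d = (1 − b) × d remains. Only a slope of 1 removes it completely.

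Section 2.2 refers to the place where therapy took place and does not say expressly where baseline is measured. Section 2.11 does not say whether the between-group test uses raw values or changes.

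**The case against.** **A stable offset may be harmless.** The last sentence of section 2.2 makes no exception for baseline, and section 2.3 speaks of changes after six weeks. If baseline is taken at the allocated facility and change is compared, or the group-by-time term of the repeated-measures analysis is used, a constant offset drops out. This stands. A reader might infer that no analysis could separate place from treatment; that goes too far. But the article does not state the condition on which the cancellation depends, and an offset that is not constant would not cancel.

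**Identical conditions may mean a standard procedure.** Section 2.10 fixes the platform model, sampling rate, task durations, the same assessor at each time point and time of day. A reader might infer that floors or platforms are known to differ; no text says so. What stands is that three locations split by arm are not identical conditions without a described common set-up. If the phrase means only consistency within a person, the arms still differ.

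**The primary outcome is instrumented.** True, and the assessor-dependent tests are tertiary outcomes. Knowledge of the arm is therefore a weaker threat to CoP area than place is. The Discussion's expectation of non-inferiority is usual in such a trial and is no evidence of assessor bias.

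**The article is silent on assessor masking.** A reader might infer that only analysts are masked. The article supports less: no assessor masking is described, and the place would defeat it.

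**Pragmatic delivery needs different places.** Delivery does; measurement need not.

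**Conclusion.** The concern holds in two parts of different strength.

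The triple-blind label is contradicted by section 2.9 and by the trainers' roles. This needs no assumption.

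Place of measurement is aligned with arm under section 2.2 as written, which conflicts with section 2.10 and reveals the arm to the assessor. A place offset would bias a between-arm comparison of post-treatment values. Its size is unknown. The rates of 7.5%, 15% and 46% at 0.25, 0.5 and 1.0 cm² show sensitivity only, and depend on assumed offsets, the planning SD of 1 cm², 8 per arm and an unadjusted t-test.

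A reader might go on to infer a false non-inferiority rate. That requires treating 1.5 as the margin, which the protocol does not say. It also requires an offset that favours TR: an offset against TR would lower power and not raise that error. The documents therefore do not support a definite figure of that kind.

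**What to change.** 1. In the abstract and section 2.1, replace the triple-blind label with the roles actually masked: participants and trainers unblinded, data analysts masked, assessor masked only if measures for this are in place. This costs nothing but wording.

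2. Replace the last sentence of section 2.2 so that both arms are assessed at all six time points at one common place on the same force platform. The two elderly centres together would not be one place. If a common place is not feasible, use the same platform with a standardised, cross-calibrated set-up at each place, take baseline where follow-up is taken, and make the between-arm comparison baseline-adjusted. Change from baseline is the form that removes a constant offset fully; a covariate alone leaves (1 − b) of it. Bring section 2.10 into line.

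3. Keep the existing assessor, on condition that this person delivers no sessions and is not told the arm, and ask participants not to reveal it.

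Cost: travel for some participants, at most 8 × 6 = 48 trips if one arm travels. Travel carries some risk of missed visits, which matters at 8 per arm. Familiarity with the test room may also remain unequal if one arm trained there. A common place reduces unblinding of the assessor but does not guarantee blinding, since participants know their arm. The sample size stays at 8 per arm.
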